## Abstract

**Background:**

Rapid access chest pain clinics have facilitated the early diagnosis and treatment of patients with coronary heart disease and angina. Despite this important service provision, coronary heart disease continues to be under-diagnosed and many patients are left untreated and at risk. Recent advances in imaging technology have now led to the widespread use of noninvasive computed tomography, which can be used to measure coronary artery calcium scores and perform coronary angiography in one examination. However, this technology has not been robustly evaluated in its application to the clinic.

**Methods/design:**

The SCOT-HEART study is an open parallel group prospective multicentre randomized controlled trial of 4,138 patients attending the rapid access chest pain clinic for evaluation of suspected cardiac chest pain. Following clinical consultation, participants will be approached and randomized 1:1 to receive standard care or standard care plus ≥64-multidetector computed tomography coronary angiography and coronary calcium score. Randomization will be conducted using a web-based system to ensure allocation concealment and will incorporate minimization. The primary endpoint of the study will be the proportion of patients diagnosed with angina pectoris secondary to coronary heart disease at 6 weeks. Secondary endpoints will include the assessment of subsequent symptoms, diagnosis, investigation and treatment. In addition, long-term health outcomes, safety endpoints, such as radiation dose, and health economic endpoints will be assessed. Assuming a clinic rate of 27.0% for the diagnosis of angina pectoris due to coronary heart disease, we will need to recruit 2,069 patients per group to detect an absolute increase of 4.0% in the rate of diagnosis at 80% power and a two-sided *P* value of 0.05. The SCOT-HEART study is currently recruiting participants and expects to report in 2014.

**Discussion:**

This is the first study to look at the implementation of computed tomography in the patient care pathway that is outcome focused. This study will have major implications for the management of patients with cardiovascular disease.

**Trial registration:**

ClinicalTrials.gov Identifier: NCT01149590

## Background

The clinical presentation of chest pain is a major problem for primary health care professionals and is the commonest medical reason for a patient attending the Emergency Department. Ascertaining the aetiology of the chest pain is essential not only for the future management and investigation of the patient, but also for health care resources to be utilized appropriately and efficiently. The distinction between cardiac and noncardiac chest pain can be subtle, leading, in some series [1,2], to between 2 and 12% of patients being inappropriately discharged from hospital and more than 25% being readmitted to hospital with benign noncardiac chest pain. From the primary care perspective, Emergency Department attendances or short-term hospitalizations with an unhelpful diagnosis, such as ‘chest pain - myocardial infarction excluded’, do not provide a clear diagnosis or management plan.

### Rapid access chest pain clinics

The accurate identification of patients with ischaemic heart disease is important because up to 30% of patients presenting with recent-onset angina have a cardiac event within 1 to 2 years [3] and many of these patients may benefit from coronary revascularization [4]. This has led many centres to develop the provision of a rapid access chest pain clinic. This out-patient clinic provides a ‘one-stop’ assessment for patients with suspected angina, including medical history, examination, electrocardiogram, blood tests, and exercise testing where appropriate. It does not include patients with acute chest pain who require immediate hospital assessment for suspected acute coronary syndrome. We have demonstrated that such services reduce the hospitalization of patients with benign noncardiac chest pain whilst facilitating the identification of those patients with acute coronary syndromes requiring in-patient care [5]. A specialist cardiology opinion combined with the resources of a chest pain clinic service would appear to have a higher diagnostic yield for ischaemic heart disease than open-access exercise electrocardiography, and would provide the primary care physician with a firm clinical diagnosis in the majority of cases, and identify those patients requiring further invasive investigation [5].

### The need for better diagnostic accuracy and risk stratification

Rapid access chest pain clinics have now become established across the United Kingdom and they have proven successful in identifying high-risk patients with coronary heart disease [6]. However, there is room for improvement, with some patients continuing to be misdiagnosed with noncardiac chest pain [6]. Moreover, those diagnosed with noncardiac chest pain account for up to a third of patients who subsequently die from cardiovascular disease or suffer an acute coronary syndrome over 5 years of follow-up [6]. There is, therefore, a need for better diagnostic accuracy and risk stratification in patients attending rapid access chest pain clinics, especially in younger patients (<65 years) [7].

### Coronary artery calcification

Coronary artery calcification is an independent risk factor for coronary heart disease, with even low coronary calcium scores doubling the risk of coronary events [8]. The relative risk associated with coronary calcification is greater than that associated with established factors, such as smoking, hypertension and diabetes mellitus. The progression of coronary artery calcification is associated with a higher incidence of coronary events, even in those people who are asymptomatic at the time of initial scanning [9]. Thus, the presence of coronary artery calcification is not only indicative of atheromatous plaque disease, but its progression may correspond with cardiovascular event rates.

The degree of calcification correlates with atheroscle rotic burden but it does not identify soft plaque and may not predict the patient’s response to medical interventions [10,11]. Moreover, the presence of coronary artery calcification does not, in itself, predict the presence of obstructive atheroma. Calcification can, therefore, be used as a surrogate marker of the extent of coronary atherosclerotic disease, rather than as a measure of luminal stenosis [12].

### Computed tomography coronary angiography

Major advances in scanning technology have led to the establishment of noninvasive coronary angiography by multidetector computed tomography (MDCT). This has a very good agreement with invasive coronary angiography [13,14] and intravascular ultrasound [13-16], with kappa coefficient values of 0.75 for both. The resolution of modern scanners allows quantification of luminal stenoses as well as identification of noncalcified ‘soft’ atherosclerotic plaque [15]. Pooled analysis of over 800 patients indicates a sensitivity of 89% (95% confidence intervals, 87 to 90%) and specificity of 96% (95% confidence intervals, 96 to 97%) for 64-MDCT in comparison with invasive coronary angiography [16]. The major strength is in the negative predictive value of 98% (95% confidence intervals, 98 to 99%). The current evolution of scanning technology has led to greater spatial and temporal resolution with lower radiation doses (~2 to 3 mSv). This should translate into a highly effective and safe imaging strategy, particularly for the evaluation of stable patients with possible coronary artery disease [17].

It is important to highlight that computed tomography (CT) coronary angiography is primarily used to confirm or refute the presence of coronary artery disease. The diagnosis of angina pectoris due to coronary heart disease primarily relies on two factors: (i) a history consistent with angina pectoris, and (ii) the presence of obstructive coronary artery disease. It should be realized that patients with coronary heart disease may have nonanginal chest pain and that patients with typical anginal chest pain may not have coronary heart disease (see Table 1).

**Table 1 T1:** Categorization of patients based on presence the presence or absence of angina pectoris and coronary heart disease

		**Coronary heart disease**	
		**Yes**	**No**
**Angina pectoris**	**Yes**	High-risk and cause of symptoms	Low-risk and cause of symptoms unclear
	**No**	High-risk but either symptoms unrelated or atypical presentation	Low-risk and other cause of symptoms likely

A health technology assessment including a comprehensive systematic review of 64-multidetector CT coronary angiography highlighted several areas that require further research, including (i) the usefulness of MDCT coronary angiography in patients with suspected coronary artery disease; (ii) the advantages of 256- versus 64-MDCT coronary angiography; and (iii) the role of MDCT to assess coronary artery plaque morphology [18]. In addition, the National Institute of Clinical Excellence (NICE) specifically called for research into the clinical efficacy and cost-effectiveness of MDCT coronary angiography compared with functional testing in the diagnosis of angina [19].

## Methods/design

### Study design

This is an open parallel group prospective randomized controlled trial, assessing the impact of CT on the diagnosis and management of patients attending a rapid access chest pain clinic.

### Study objectives

The purpose of a rapid access chest pain clinic is to identify patients with symptoms of angina attributable to coronary heart disease, in order to identify those who would benefit from secondary prevention and anti-anginal therapies. The standard approach is to document a clinical history of angina pectoris and demonstrate objective evidence of exercise-induced myocardial ischaemia through exercise stress testing. We wish to evaluate the added value of coronary artery calcium scoring and CT coronary angiography in the assessment of patients attending a rapid access chest pain clinic.

In the setting of a rapid access chest pain clinic, the most important question that the patient has is whether his or her chest pain is due to coronary heart disease. The primary objective of the study, therefore, is to investigate whether the inclusion of coronary artery calcium scoring and CT coronary angiography alters the proportion of patients diagnosed with angina due to coronary heart disease at 6 weeks.

The secondary objectives of the study are to ascertain whether a coronary artery calcium score and CT coronary angiogram influences the management of patients with coronary heart disease or noncardiac causes of chest pain. Patients’ concerns often relate to the chest pain itself (symptoms), what causes their symptoms (diagnosis), what further tests are required (investigations), what medication or procedures are recommended (treatments) and what the impact will be on their future health (long-term outcomes). We will also assess safety and health economic outcomes. We will undertake long-term follow of these patients to determine whether CT assessments independently predict future risk, and whether this leads to improved clinical outcomes through better guided use of therapies.

### Primary endpoint

The primary endpoint of the study will be the proportion of patients diagnosed with angina pectoris secondary to coronary heart disease at 6 weeks. The clinician in charge of the patients’ care will assign the diagnosis following either (a) analysis of the coronary artery calcium score and CT coronary angiogram (intervention group), or (b) standard care (conservative group).

### Secondary endpoints

The following secondary endpoints will be evaluated: (i) the frequency and severity of chest pain symptoms at six weeks and six months; (ii) the CT observed presence and extent of coronary artery disease; (iii) the diagnosis and severity of coronary heart disease; (iv) the accuracy of CT coronary angiography compared with the gold-standard of invasive coronary angiography in those who receive both investigations; (v) the effect on investigations, unscheduled care and healthcare resource utilization; and (vi) the effect on patient management, including secondary prevention, anti-anginal therapy (pharmacological therapy and coronary revascularization), and treatment of noncardiac chest pain (such as hiatus hernia).

The study has been primarily set up to assess a patient-focused symptom outcome. However, alterations in management may result in long-term benefits to patients. Therefore long-term outcomes will be assessed, including: (i) cardiovascular death or nonfatal myocardial infarction; (ii) cardiovascular death; (iii) nonfatal myocardial infarction (universal definition); (iv) cardiovascular death, nonfatal myocardial infarction or nonfatal stroke; (v) nonfatal stroke; (vi) all causes of death; (vii) coronary revascularization, percutaneous coronary intervention or coronary artery bypass graft surgery; (viii) hospitalization for chest pain, including acute coronary syndromes and noncoronary chest pain; and (ix) hospitalization for cardiovascular disease, including coronary artery disease, cerebrovascular disease and peripheral arterial disease.

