### Randomization

Following recruitment, patients who agree to undergo research evaluation will be randomized (1:1), either to no additional scanning or to undergo further evaluation with coronary calcium scoring and CT coronary angiography within 14 days of clinic attendance and before invasive coronary angiography or other cardiac investigations. Randomization will be conducted using a web-based system to ensure allocation concealment and will incorporate minimization to ensure matching for age, sex, body mass index (height and weight), diabetes mellitus, prior history of coronary heart disease, atrial fibrillation and baseline diagnosis of angina due to coronary heart disease.

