### Study assessments and data collection

#### Clinic assessment

All patients will undergo routine evaluation at the rapid access chest pain clinic including, where appropriate, symptom-limited exercise electrocardiography using the standard Bruce protocol. Patients will be categorized as low, intermediate or high risk by the attendant clinician, informed by the NICE guideline [20]. In general, high-risk patients will be treated for coronary heart disease and undergo invasive coronary angiography (10%), and low-risk patients (10%) will be reassured and discharged. Intermediate-risk patients (80%) will be treated and further investigated at the discretion of the clinician. In all cases, the diagnosis and agreed management strategy will be documented at the end of the clinic attendance. Cardiovascular risk will be calculated using previously established risk scores, such as the ASSIGN and Framingham scores.

The study data sheet will be used in the rapid access chest pain clinic to document patient history, examination and management plan for all patients (recruited and unrecruited). This will be completed by the attending clinician or nurse. This will also include assessment of eligibility. The study pro forma for all ineligible participants and eligible unrecruited participants will be retained in an anonymized form to provide detailed data on these patients in comparison with the study participant population. All study pro formas (recruited and unrecruited eligible and ineligible patients) and consent forms (recruited participants) will be collated by the trial manager and entered into the database.

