### Diagnostic outcomes

The proportion of patients diagnosed with coronary heart disease will be documented at baseline, after CT (where appropriate), after 6 weeks and after 6 months. This will be defined as (i) prior history of coronary heart disease (previous documented acute myocardial infarction (universal definition), obstructive coronary heart disease (≥70% luminal stenosis in at least one major epicardial vessel on invasive coronary angiography) or previous coronary revascularization (percutaneous coronary intervention or coronary artery bypass surgery)), (ii) clinical diagnosis of angina pectoris due to coronary heart disease, or (iii) obstructive or nonobstructive CT diagnosis of coronary heart disease. The extent of coronary heart disease will be determined by the number of vessels affected (none, one, two or three vessels diseased (≥70% luminal stenosis of a major epicardial vessel)) and plaque load determined by CT coronary angiography.

The accuracy of the CT coronary angiography will be determined by comparison with invasive coronary angiography (gold-standard) for the assessment of the number of vessels affected. The extent of plaque burden cannot be compared between the two modalities.

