### Investigation outcomes

Relevant investigations will be documented for each participant at the baseline clinic attendance, after 6 weeks and after 6 months. This will include: an exercise electrocardiographic stress test; nuclear medicine imaging - myocardial perfusion imaging; stress echocardiography; invasive coronary angiography; and noncardiac investigations, for example, endoscopy.

This will be documented by the clinician in charge of patient care in response to the CT coronary angiogram report. Further information will be obtained from electronic hospital records and patient surveys. Computed tomography coronary angiography will be performed prior to any invasive coronary angiogram, to facilitate a decision to undertake or cancel this invasive investigation.

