### Diagnosis and management documentation

The CT scan report will include a section requesting the documentation of any changes in the diagnosis, investigation and treatment of the participant. The chest pain clinic nurse or responsible consultant will complete this pro forma and return it to the trial manager.

At 6 months, trial and data manager will document changes in patient diagnosis, investigation and treatment for all patients at 6 weeks and 6 months using the TrakCare™ software application (InterSystems Corporation, Cambridge, MA, USA), which is an electronic patient record system used by the National Health Service (NHS) Lothian Health Board. This system is destined to be adopted by other centres throughout Scotland. Where appropriate, this will be supplemented by source document review.

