## Discussion

The multicentre randomized controlled SCOT-HEART trial will assess the added value of CT imaging in over 4,000 patients attending rapid access chest pain clinics. This will define the most appropriate use of this emerging technology in the setting of diagnosing and treating patients with coronary heart disease and angina pectoris. This study will also lay the foundation for future studies to look at the potential prognostic value of this technology.

Current opinion suggests that the main utility of CT coronary angiography lies with the diagnosis and management of patients at intermediate risk of coronary heart disease [12,20] although recent evidence suggests that it may have a role in the care of patients with suspected acute coronary syndrome [31]. However, it could have a role even in apparently high-risk patients with stable symptoms, since CT may help identify patients with ‘false-positive’ stress tests that could potentially avoid invasive coronary angiography. Alternatively, it may allow early identification of patients at high risk of invasive coronary angiography (such as critical left main stem stenosis), those with anomalous coronary anatomy, or those for whom coronary revascularization is likely to be necessary. In the latter scenario, this will facilitate planning of invasive angiography and allow an interventional cardiologist to undertake follow-on percutaneous coronary intervention as required. This would potentially avoid the need for recurrent invasive angiography in situations where a noninterventional cardiologist performs the diagnostic angiogram.

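### CT accuracy is measured only in patients who go on to invasive angiography, a step the CT result helps decide, so raw accuracy figures are open to partial verification bias

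*Protocol article*

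**What the plan says.** Under Secondary endpoints, item (iv) is "the accuracy of CT coronary angiography compared with the gold-standard of invasive coronary angiography in those who receive both investigations". The section Diagnostic outcomes takes this up and says "The accuracy of the CT coronary angiography will be determined by comparison with invasive coronary angiography (gold-standard"), the quantity compared being the number of vessels affected. The limitation to patients with both tests is not repeated there.

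The order of the tests is fixed. Randomization places the scan within 14 days of the clinic visit and "before invasive coronary angiography or other cardiac investigations". Investigation outcomes gives the reason: "Computed tomography coronary angiography will be performed prior to any invasive coronary angiogram, to facilitate a decision to undertake or cancel this invasive investigation". The same link shows in the sentence "The CT scan report will include a section requesting the documentation of any changes in the diagnosis, investigation and treatment of the participant" (section Diagnosis and management documentation) and in the Discussion, which expects CT to pick out patients with false-positive stress tests "that could potentially avoid invasive coronary angiography".

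CT is not the only influence on referral. Under Clinic assessment, high-risk patients (10%) generally go to invasive angiography, low-risk patients (10%) are generally discharged, and further investigation of intermediate-risk patients (80%) is left to the clinician. Image assessment provides for the two angiograms to be read independently, each without knowledge of the other.

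**The concern.** The reference test is available only for patients sent to it, and the test being evaluated helps to decide who is sent. When a negative CT makes invasive angiography less likely, two groups are under-counted. Patients with disease that CT missed are seldom verified, so false negatives go unseen. Patients whom CT correctly cleared are also seldom verified, so the specificity denominator loses true negatives. Blinded reading prevents one reading from influencing the other, but it cannot bring back patients who never had the reference test.

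What is at stake is the meaning of a secondary result. A reader would naturally set the trial's accuracy figures beside the 89% sensitivity and 96% specificity quoted in the Background. A raw figure from referred patients does not estimate the same quantity as accuracy in everyone scanned.

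**Working it through.** **The plan's own figures.** The article states no target or sample size for the accuracy endpoint, so there is nothing to reproduce for it. The number scanned, 2,069 per group, comes from the primary endpoint. It reproduces exactly for 27.0% against 31.0% at 80% power and two-sided 0.05 with continuity correction (2,019 without).

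**Inputs.**
- Se = 0.89 and Sp = 0.96, from the Background section on CT coronary angiography, taken here as true.
- v+ and v−, the shares of CT-positive and CT-negative patients who have invasive angiography. These are assumed. I hold v+ at 0.80 and vary v−.
- Prevalence of obstructive disease, also assumed: 15% (roughly what the cited negative predictive value of 98% implies) to 27%. It is needed only for counts and overall accuracy.

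**Formulas, if referral depends on CT alone.**
- Apparent sensitivity = Se·v+ / [Se·v+ + (1−Se)·v−]
- Apparent specificity = Sp·v− / [Sp·v− + (1−Sp)·v+]

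Prevalence cancels from both. With v− = 0.10, sensitivity = 0.712 / (0.712 + 0.011) = 98.5% and specificity = 0.096 / (0.096 + 0.032) = 75.0%.

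| v+ | v− | Apparent sensitivity | Apparent specificity |
|---|---|---|---|
| 0.80 | 0.80 | 89.0% | 96.0% |
| 0.80 | 0.40 | 94.2% | 92.3% |
| 0.80 | 0.20 | 97.0% | 85.7% |
| 0.80 | 0.10 | 98.5% | 75.0% |
| 0.80 | 0.05 | 99.2% | 60.0% |

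**Overall accuracy.** At v− = 0.10 it reads 86.7% against a true 95.0% (prevalence 15%), or 90.9% against 94.1% (prevalence 27%).

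**Precision.** At v− = 0.10 and prevalence 15%, the CT-positive share is 0.15×0.89 + 0.85×0.04 = 0.1675. About 2,069 × (0.1675×0.80 + 0.8325×0.10) = 449 patients are verified. Expected verified false negatives are 2,069 × 0.15 × 0.11 × 0.10 = 3.4.

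**Referral that also depends on clinic risk.** Assume that the 10% high-risk patients are all verified (prevalence 60%) and that the other 90% follow CT with v+ = 0.80 and v− = 0.05 (prevalence 22%). As fractions of all scanned patients, the verified cells are:
- TP = 0.0534 + 0.1410 = 0.1944
- FN = 0.0066 + 0.0011 = 0.0077
- FP = 0.0016 + 0.0225 = 0.0241
- TN = 0.0384 + 0.0337 = 0.0721

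Apparent sensitivity is 96.2%, specificity 75.0% and overall accuracy 89.4% (true 94.2%). The negative predictive value among verified patients is 0.0721 / 0.0798 = 90.4%. The true value at overall prevalence 0.258 is 0.7123 / 0.7407 = 96.2%.

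**What a correction does.** Begg-Greenes applies the predictive values found in verified patients to the CT results of everyone scanned. Where referral depends only on CT, it returns 89% and 96% in every row of the table. In the mixed case it must be done within risk strata. Pooled over risk, it gives sensitivity 0.2593×0.8898 / (0.2593×0.8898 + 0.7407×0.0964) = 0.2307 / 0.3021 = 76.4%, an over-correction. Within each stratum referral depends only on CT, so the stratified version recovers the truth.

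**The case against.** The strongest reply is that the article names a population and a reference standard but no estimator, and leaves the analysis to a separate plan that may contain a correction. The words limiting endpoint (iv) to patients with both tests are also an honest qualifier. Part of this stands: the absence of a named correction is not itself a fault. But the article does fix the restricted population and the CT-informed referral, and Diagnostic outcomes then speaks of CT accuracy with no restriction. The qualifier says who is counted, not that the CT result helped to select them.

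The objections on size stand. CT informs referral alongside clinic risk and clinician discretion, no verification rates are given, and at 80%/40% the distortion is modest. It also stands that the named measure is the number of vessels, so the two-by-two arithmetic illustrates the mechanism rather than that measure itself.

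A reader might infer more than the documents support:
- That CT alone decides who has invasive angiography. The article says it helps the decision.
- That the trial will report near-perfect sensitivity and poor specificity whatever the truth. That depends on assumed rates.
- That biased accuracy figures will enter the economic decision model. The health economic section brings in within-trial analyses but does not name CT accuracy as an input.
- That predictive values among verified patients are safe. The mixed case shows that they need not be.

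**Conclusion.** The point holds as a minor one about a secondary endpoint. Provided CT-positive patients are referred more often than CT-negative ones, which is the stated purpose of scanning first, raw sensitivity for obstructive disease is biased upward and raw specificity downward. Agreement on vessel count is subject to the same selection; its size has not been worked out here. The direction follows from the design. The magnitude does not: over the assumed range it runs from no bias with equal verification to 99.2% and 60.0% at 80%/5%, taking 89% and 96% as true. The primary comparison of the randomized groups does not use these figures and is unaffected.

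**What to change.** Keep endpoint (iv) and leave referral as it is.

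1. In Secondary endpoints and Diagnostic outcomes, state that raw accuracy figures, including predictive values, describe only patients referred for invasive angiography after CT, and that they are not directly comparable with the figures in the Background.
2. Add an estimate for all scanned patients, for obstructive disease (yes/no) and, where data allow, for vessel count. Use stratified Begg-Greenes or inverse-probability-of-verification weighting, conditional on CT result, clinic risk category and baseline diagnosis. Clinic risk category and diagnosis are already recorded under Clinic assessment, and baseline diagnosis is a minimization factor.
3. Report the number verified in each CT-by-risk stratum, and give bootstrap intervals.
4. Do not make predictive values among verified patients the main summary unless they are also adjusted for clinic risk.

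The cost is wording and a short analysis, with no new patients, tests or data. The drawbacks are wider intervals, reliance on verification depending only on recorded variables, and possibly very few verified patients in low-risk CT-negative strata. The counts in step 3 would show where the data are too sparse.
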